## 3. Procedure

### 3.1. Sampling and Recruitment

A multi-stage sampling method will be used in this study. Stage 1 will involve the sampling of sub-counties, stage 2 will involve the sampling of schools, participant selection will be performed in stage 3, and stage 4 will involve the sampling of embedded sand-fleas.

Stage 1: Sampling of sub-counties:

Ndhiwa and Suba South sub-counties will be sampled because they have the highest number of reported cases of tungiasis in Homa Bay County. 

Stage 2: Sampling of schools:

Primary schools in the study area are ranked according to the number of reports made to the Health Department. Therefore, we will visit schools in areas with the highest number of reported cases and with the highest number of affected students, in order. 

Stage 3: Sampling of participants:

In each school, children aged 8 to 14 years will be selected in descending order of grade. At the beginning of the study, a sealed envelope will be used to randomise the two treatments. In the sealed envelopes will be written “Right foot: dimeticone, Left foot: 5% sodium carbonate” or “Right foot: 5% sodium carbonate, Left foot: dimeticone” with a participant number. Before randomisation, lesions will be sampled to avoid selection bias.

Children will be informed not to manipulate the lesions during the next 7 days. Children whose skin conditions are suspected to be due to tungiasis by teachers, caregivers, and healthcare workers (including community health-volunteers) will be screened for eligibility to participate in this study. Such children and their caregivers will then be contacted by the local co-investigator and their field assistants to ask if they are willing to participate in the study, after explaining the study objectives and procedures. Informed consent from caregivers and assent from children will be obtained after both agree to participate. Participants will be randomly selected until the point of saturation is reached.

Stage 4: Sampling of embedded sand-fleas:

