### 4.1. Statistical Analysis

For the primary outcome, logistic regression analysis (stepwise regression) will be performed, because it is binary. Since all secondary outcomes are score data, they are continuous measures; thus, analysis of covariance will be performed using two variables (sex (male or female) and footwear use (shoes or sandals)) as covariants. This is because previous studies have shown that the male sex is a risk factor for tungiasis, and that the thickness of the skin of the foot may change depending on whether sandals are used, which may affect the penetration of the treatment [32]. We will use generalized estimating equations for side effects such as pain and itching, to consider relative risks. The per-protocol set, which analyses only subjects who adhere to treatment, is more likely to show superiority or a significant increase in risk, while the intention-to-treat analysis is more likely to show non-inferiority with or without significant differences. Therefore, a per-protocol approach will be adopted for this non-inferiority study. All data will be analysed using EZR version 1.60 (Jichi Medical University Saitama Medical Center, Saitama, Japan). Missing values will be imputed using the multiple-imputation method. For the main analysis, we will use one-sided *p*-values at an *α* = 0.025 level of significance; for others, we will use two-sided *p*-values at an *α* = 0.05 level of significance.

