### 4.5. Hazards and Risks Associated with the Study

If improperly handled, or in the event of accidental exposure, sodium carbonate can pose some hazards to health and safety. If participants experience adverse effects such as irritation, blisters, or burning sensation (which generally happens when a concentrated substance gets into the eyes or is inhaled), we will immediately flush the skin with plenty of water and provide necessary treatments or refer the participant free of charge to the nearest health facility.

Another possible risk is that the child may be teased for having jiggers, since this will be revealed to other children in the school by participation in the study. Before selecting participants, we will provide information on tungiasis through health promotion, so that all children will have proper understanding, to reduce prejudice, discrimination, or stigmatisation toward people affected with the disease. By so doing, we aim to minimise the mental burden on participants. In addition, confidentiality will be maintained throughout the study. Any severe adverse reactions (such as dermatitis, fever, and headache) and events occurring during the follow-up period will be recorded and considered for potential association with the treatment.

In the case that treatment is needed at a doctor’s discretion, participants will be immediately referred to the hospital for treatment, and if the treatments show no effect they will be stopped immediately, before study completion. The treatment will be applied not only to the lesions to be studied but also to other identified lesions. In addition, excluded participants (such as people with embedded sand-fleas on only one foot) will be treated with the agent that works best when the intervention is completed.

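### The per-protocol set alone decides non-inferiority, on a general rule that is unsafe if children or lesions leave that set because treatment failed

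*Protocol article*

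**What the plan says.** Section 4.1 (Statistical Analysis) describes the set by adherence: "The per-protocol set, which analyses only subjects who adhere to treatment". It rejects the alternative because "the intention-to-treat analysis is more likely to show non-inferiority with or without significant differences", and concludes: "Therefore, a per-protocol approach will be adopted for this non-inferiority study". No intention-to-treat, co-primary or sensitivity set is named. For the main analysis "we will use one-sided *p*-values at an *α* = 0.025 level of significance". On missing data: "Missing values will be imputed using the multiple-imputation method".

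Three other statements bear on who might leave the set:

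- Section 4.5 (Hazards and Risks) says that where a doctor judges treatment necessary, "participants will be immediately referred to the hospital for treatment".
- The same sentence goes on: "if the treatments show no effect they will be stopped immediately, before study completion".
- Section 3.1 (Sampling and Recruitment) says: "Children will be informed not to manipulate the lesions during the next 7 days".

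None of these says whether the children or lesions concerned stay in the per-protocol set, or how they are scored at day 7.

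**The concern.** Per-protocol is often the stricter set for non-inferiority, because poor adherence blurs real differences under intention-to-treat. That argument needs departures that are unrelated to outcome. Here nurses apply both treatments in person (sections 3.2 and 3.3), so ordinary non-adherence should be rare. Most departures would arise after treatment, and the two routes in section 4.5 can depend on how the lesion is doing. A unit stopped for lack of effect is a likely failure of the primary endpoint.

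If failures leave the set, the worse arm has more of them to lose, so the observed gap narrows even when both feet lose the same share. A set formed after treatment is not protected by randomisation, and it is the only set on which the decision rests. Section 4 hopes the result will help bring new treatments into national guidelines, so a false claim of non-inferiority would matter.

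The article fixes this choice and gives its reason. It is therefore not a detail left open for a fuller document.

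**Working it through.** **1. The plan's own figure.** Inputs from section 2.8: cure 80% in both arms, margin 10 points, 90% power, α = 0.05, design effect 1.5, 10% loss.

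- n per arm = (1.6449 + 1.2816)² × 2 × 0.80 × 0.20 / 0.10² = 8.564 × 32 = 274.1, rounded up to 275
- × 1.5 = 412.5, rounded up to 413
- / 0.90 = 458.9, rounded up to 459

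The plan states 460, so the figure reproduces with α = 0.05 taken as one-sided. (The main analysis uses one-sided 0.025. That mismatch is a separate matter and is not used here.) After the planned loss, 460 × 0.9 = 414 evaluable lesions per arm.

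**2. Effect of losing failures.** Assumed true cure: carbonate 70%, dimeticone 80%, so the true difference is exactly −10 points. If a share f of failed lesions leaves an arm with cure rate p:

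per-protocol cure = p / (1 − f(1 − p))

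False non-inferiority rate = Φ((d + 0.10)/SE − 1.96), where d is the per-protocol difference. SE is the unpooled standard error on the lesions remaining out of 414, divided by the design effect of 1.5. Pairing of feet within a child is ignored beyond the design effect.

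Example, f = 20% on both feet:

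- Carbonate 0.70/0.94 = 0.7447; dimeticone 0.80/0.96 = 0.8333; d = −0.0887
- Effective numbers 414 × 0.94/1.5 = 259.4 and 414 × 0.96/1.5 = 265.0
- SE = √(0.7447 × 0.2553/259.4 + 0.8333 × 0.1667/265.0) = 0.0355
- Φ(0.32 − 1.96) = 5.1%

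| Failures lost, carbonate / dimeticone | Lesions lost | Per-protocol cure | Difference (points) | False non-inferiority |
|---|---|---|---|---|
| 0% / 0% | 0% / 0% | 70.0% / 80.0% | −10.0 | 2.5% |
| 10% / 10% | 3% / 2% | 72.2% / 81.6% | −9.5 | 3.5% |
| 20% / 20% | 6% / 4% | 74.5% / 83.3% | −8.9 | 5.1% |
| 30% / 30% | 9% / 6% | 76.9% / 85.1% | −8.2 | 7.6% |
| 10% / 0% | 3% / 0% | 72.2% / 80.0% | −7.8 | 8.6% |
| 20% / 0% | 6% / 0% | 74.5% / 80.0% | −5.5 | 23% |
| 10% / 20% | 3% / 4% | 72.2% / 83.3% | −11.2 | 1.1% |

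Starting from all 460 lesions instead of 414, the 20%/20% and 30%/30% rows give 5.2% and 8.0%.

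**3. If whole children leave.** Section 4.1 words the set by subject, so both feet may leave together. Let q be the probability that both feet are cured, and let a share f of children with any failed foot leave. Then

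difference = (1 − f)(−0.10) / (1 − f(1 − q))

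With f = 20%: −0.08/0.912 = −8.8 points at q = 0.56, and −0.08/0.93 = −8.6 points at q = 0.65. The gap still narrows.

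**4. When there is no bias.** Exclusions unrelated to outcome leave both rates unchanged. If true cure rates are equal and the same share of failures leaves each foot, both rates rise equally and the difference stays at zero.

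**The case against.** The strongest reply is that the text never says failures leave the set. It is defined by adherence. Treatment is given by nurses at the intervention and no later application is described, so a fully treated lesion that fails is adherent and stays. On that reading the per-protocol set is close to all treated lesions and the bias is near zero. The stopping sentence in section 4.5 is plural, sits in a hazards section, and can be read at treatment, child or whole-study level. This stands as a limit: the documents leave the handling open, and the bias is conditional on how it is settled.

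A reader might infer that the per-protocol choice simply biases the trial toward non-inferiority, and by a lot. If 5% of all carbonate-foot lesions are failures that leave and none leave on the other foot, the difference is 0.70/0.95 − 0.80 = −6.3 points. At 8% it is 0.70/0.92 − 0.80 = −3.9. A true −12 with 5% lost appears as 0.68/0.95 − 0.80 = −8.4. The documents do not support one-sided loss as the expected case. Applying the same share of failures to both feet gives:

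- 0.70/0.95 − 0.80/0.967 = −9.1
- 0.70/0.92 − 0.80/0.947 = −8.4
- true −12: 0.68/0.95 − 0.80/0.969 = −11.0, still beyond the margin

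A reader might also infer that manipulated lesions are failures dug out because they hurt. The article says only that children are told not to manipulate them. A removed flea shows none of the four viability signs in section 2.6 and could be scored as cured, so excluding it could work against carbonate or for it. The direction is not shown.

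Nor can it be said that multiple imputation removes failures. Viability is recorded on days 3 and 5, and a model using those visits could carry early failure forward. The article does not specify the model.

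What the reply does not rescue is the stated rationale. It is offered as a general rule, and it fails when departures follow failure.

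**Conclusion.** The concern holds in conditional form. The article makes per-protocol the sole basis for the decision on a rule that is unsafe here, and its own wording on referral and stopping leaves room for failure-related departures whose handling is not stated. If such units leave at a similar rate on both feet, or more often on the carbonate foot, the difference is biased toward non-inferiority when carbonate is truly worse.

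With similar loss on both feet the effect is moderate: at 20% to 30% of failures lost, false non-inferiority is roughly two to three times the nominal 2.5%. One-sided loss on the carbonate foot would do more harm, and heavier loss of dimeticone failures would make the test too strict.

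These sizes rest on assumed cure rates of 70% and 80%, assumed exclusion shares, 414 evaluable lesions per arm, a design effect of 1.5 and a normal approximation. The plan should be changed, because the remedy is cheap and protects the conclusion. The documents do not show that the result will be biased.

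**What to change.** Amend section 4.1 as follows:

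- Analyse all randomised lesions that were viable at baseline, on their allocated foot, as co-primary with the per-protocol set. Claim non-inferiority only if the lower 95% bound exceeds −10 points in both.
- In the all-randomised set, count lesions extracted, given other treatment or stopped for no effect before day 7 as not cured. In the table's scenarios, if the lesions that left are kept and counted this way, the difference stays at −10 points and the false rate at 2.5%.
- Use multiple imputation, with the day 3 and day 5 viability results in the model, only for visits missed for other reasons. Add a sensitivity analysis that counts missing carbonate-foot lesions as not cured.
- State whether exclusion from the per-protocol set acts on the lesion, the foot or the child, and at what level the stopping sentence in section 4.5 applies.

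No clinical rule needs to change. The cost is analysis wording, one extra analysis and a slightly lower chance of a non-inferiority claim. If few such departures occur, the two sets will nearly coincide and little is lost.

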### 4.2. Monitoring Plan for the Study

An independent monitor will oversee the study, apart from the data and safety monitoring committee, which consists of several team members. This is because this study is relatively small-scale, with treatments already locally used, and there is little possibility that significant safety problems will occur. The monitor will confirm the appropriate implementation of the study, proper recording of necessary items, and data reliability. Specifically, the monitor will review the research protocol, informed consent form, questionnaire, records of observations and follow-ups, and observe the drugs to be used. Again, at the study site, the monitor will observe any deviation from the research protocol, protect the rights and safety of the participants, and advise correction if any problems arise. The monitor will also propose a decision to terminate the study when serious adverse effects/events occur or when a significantly superior effect is confirmed in one treatment group by the interim analysis. 

### 4.3. Early Termination of the Study (Stopping Rule)

Due to the difficulty of proper evaluation in the middle of a study and information bias resulting from continuation, we do not consider it necessary to conduct an interim analysis for this short-term, low-risk study.

### 4.4. Adverse Events/Effects

All adverse events, whether serious or non-serious, will be recorded until day 7, which is the end of the study, after the participant and his/her caregivers have provided assent and consent and enrolled in the study. If a participant experiences an adverse event after the informed-assent and consent forms are signed, but the participant has not started to receive the study intervention, the event will be reported as unrelated to the study treatments. A serious adverse event for this study is defined as any untoward medical occurrence that is believed by the investigators to be causally related to the study treatments and results in any of the following: a life-threatening condition with an immediate risk of death, severe or permanent disability, and prolonged hospitalisation. Serious adverse events occurring after a participant discontinues the study will not be reported unless the investigators feel that the event may have been caused by the study drugs or a protocol procedure. The investigators will determine the relatedness of an event to the study treatment, based on a temporal relationship to the study treatment and whether the event is unexpected or unexplained given the participant’s clinical course, previous medical conditions, and concomitant medications. All adverse events will be assessed as part of routine monitoring. Any adverse event that can be attributed to the intervention will be specified as a secondary outcome. However, we cannot know which treatment might cause adverse effects with general symptoms such as fever and high blood-pressure, since all participants will receive both treatments. Therefore, those general symptoms will be checked for the safety of the study and to provide information for a doctor to judge whether to continue the research; other acute pathologies, such as skin symptoms, can be analysed by each treatment.

The study will carefully evaluate the safety and harm of the interventions, specifically, the quality and proper preparation of 5% sodium carbonate and dimeticone, and the procedure for applying these solutions to the participants’ feet. The principal investigator or co-investigators will follow any clinically significant abnormalities until resolution or until a clinically stable endpoint is reached. 

If any participant should react to the study treatment, the study nurses will detect it and take the child to the nearest health facility, a subcounty or county hospital, for appropriate care. 

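### The serious adverse event definition requires a causal belief and names neither death nor a new admission, so some grave events fall outside the monitor's termination trigger

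*Protocol article*

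**What the plan says.** Section 4.4 (Adverse Events/Effects) sets two conditions for a serious adverse event, and both must be met. The first is causal: the event is "any untoward medical occurrence that is believed by the investigators to be causally related to the study treatments". The second is an outcome, any one of the following: "a life-threatening condition with an immediate risk of death, severe or permanent disability, and prolonged hospitalisation".

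The same section also contains these rules:

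- Relatedness is a determination in its own right, made on timing and on whether the event is otherwise explained: "The investigators will determine the relatedness of an event to the study treatment".
- Events after discontinuation carry a further condition: "Serious adverse events occurring after a participant discontinues the study will not be reported unless the investigators feel" that a study drug or a study procedure may be the cause.
- Recording is broad: "All adverse events, whether serious or non-serious, will be recorded until day 7".
- General symptoms are checked partly "to provide information for a doctor to judge whether to continue the research".

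Section 4.2 (Monitoring Plan for the Study) uses the category: "The monitor will also propose a decision to terminate the study when serious adverse effects/events occur". The only other ground it gives for such a proposal is a clearly superior result at an interim analysis, which section 4.3 says is not thought necessary.

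**The concern.** Seriousness describes how bad the outcome was. Relatedness is an opinion about why it happened. If the opinion is a condition of entry to the serious category, an event judged unrelated leaves that category whatever its outcome. The investigators' judgement then acts before the independent monitor's trigger can.

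The outcome list has a second gap. Death is not named, and a hospital stay counts only if it is prolonged. Sections 4.4 and 4.5 provide for children who react to treatment to be taken or referred to a health facility or hospital, so a short admission is a foreseeable event in this study.

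What is at stake is which events are labelled serious, and which of them count towards the monitor's proposal to terminate a trial in children aged 8 to 14.

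**Working it through.** No arithmetic applies, because the point concerns the wording of a rule. The check applies the section 4.4 definition to plausible events, carries the result to section 4.2, and then compares the definition with the rest of section 4.4.

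**Step 1. Apply the two conditions.**

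| Event | Causal condition | Outcome condition | Serious under 4.4? | Within the 4.2 trigger? |
|---|---|---|---|---|
| Death, judged unrelated | fails | not named | no | no |
| Life-threatening event, judged unrelated | fails | met | no | no |
| Short new admission, judged related | met | fails, not prolonged | no | no |
| Death, judged related | met | not named; enters only if read into the life-threatening item | by interpretation | by interpretation |
| Long new admission, judged related | met | arguably met | probably | probably |
| Life-threatening event, judged related | met | met | yes | yes |

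The first three rows are the clear gaps. The next two depend on how the list is read. Only the last is unambiguous.

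**Step 2. Look for another definition.** Sections 4.2 to 4.5 give none. Section 4.2 uses the term without defining it, so the only definition that the article supplies for the trigger is the one in section 4.4.

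**Step 3. Compare section 4.4 with itself.**

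- The section has investigators decide relatedness as a step of its own. For a serious event that step has nothing left to decide, because the label already presupposes a causal belief.
- The section withholds serious events after discontinuation unless a causal link is thought possible. If every serious event is already believed causal, that condition excludes nothing.
- The discontinuation clause accepts a study procedure as a possible cause. The definition mentions only the study treatments.

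The first two rules make sense only if an event can be serious without being judged related, which the definition rules out. The third shows that the two causal tests do not cover the same causes.

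**The case against.** The strongest reply is that the serious label is not the only safety route. All adverse events are recorded to day 7. The monitor reviews the observation and follow-up records, protects participants' safety and advises correction. A doctor can judge continuation from general symptoms. Section 4.5 has severe reactions and events recorded and considered for a link to treatment. None of this requires the serious label, and section 4.2 does not cite the section 4.4 definition. This reply stands in part: the information is kept and people are assigned to look at it. It does not restore the classification, and the monitor's stated ground for proposing termination still uses a term that the article defines only in section 4.4.

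It is also fair that a related death would naturally be read into the life-threatening item, and that a separate relatedness judgement already exists. The first narrows the gap to unrelated deaths and other events judged unrelated, and to short admissions. The second makes the repair smaller.

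A reader might infer more than the text supports:

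- **That the split-foot design weakens the causality test.** Section 4.4 does say "we cannot know which treatment might cause adverse effects with general symptoms such as fever and high blood-pressure". That concerns which of the two agents is responsible. The definition asks about the study treatments together, so an event caused by either one meets it.
- **That unblinded investigators make the judgement.** Section 3.2 makes the principal investigator a blinded observer; the unblinded staff are those who give the treatment. The defect does not depend on blinding.
- **That the safety objective is under-counted.** Objective 2 in section 2.1 concerns the incidence of adverse effects, and section 2.6 lists these as symptoms. They are recorded whether or not the event is called serious.
- **That the size of the trial gives the size of the problem.** The number of children enrolled says nothing about how often serious events occur, and the article gives no rate.

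**Conclusion.** The point holds as a defect in classification and in the trigger that relies on it. As written, a death or life-threatening event judged unrelated is not serious, nor is a short new admission even when judged related, and none of them sets off the termination proposal in section 4.2. Section 4.4 is also inconsistent with its own relatedness step and its discontinuation clause. This is a rule that the article states outright, not detail left to a fuller document.

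The size cannot be put as a number. The practical effect may be nil if no such event occurs in a seven-day topical study. The primary analysis, the adverse-effect endpoint and the record of events to day 7 are not affected.

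The conclusion rests on two assumptions: that section 4.2 uses the term in the section 4.4 sense, since no other definition is given, and that a short new admission is not a prolonged one. If the monitor in practice applied a broader meaning, the trigger would work better than the text says, but the text would still need correcting.

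**What to change.** In section 4.4, define a serious adverse event by outcome regardless of cause: death, a life-threatening event, a new or prolonged inpatient admission, or persistent or significant disability. Remove the causal clause from the definition. Keep relatedness as the separate judgement that the section already describes, and record it as its own field on the adverse event form. Send every serious event to the monitor together with its relatedness.

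Reconcile sections 4.2 and 4.4 so that the monitor's trigger refers explicitly to the definition. Review the discontinuation clause so that its causal condition, and its mention of study procedures, agree with the new wording. These changes concern classification and reporting; what should lead to termination remains for the sponsor and monitor to settle.

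The cost is about two sentences in section 4.4, a cross-reference in section 4.2 and one form field if relatedness is not already captured. A few more events will be reported as serious, some of them unrelated to treatment.

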NYDA^®^ contains two dimeticones or silicone oils with different viscosities and a high creeping property. In many European countries, it is commercialised as a medicinal product for the treatment of head-lice infestation, and is produced by G. Pohl-Boskamp GmbH & Co. KG, Hohenlockstedt, Germany [20,21]. The extremely low viscosity (100 cSt) of NYDA^®^ enables it to penetrate the trachea (respiratory airways) and thereby suffocate the embedded insect. Dimeticones are safe, since they are biochemically inert, non-toxic, non-carcinogenic, and non-teratogenic [22,23]. Due to the physical mode of action of dimeticones, it is highly unlikely that sand fleas would develop resistance. The only disadvantage of the agents is that they are inflammable; thus, it is recommended that individuals should stay away from fires for up to 2 h after application [24].

This is the research protocol: in this study, we compare experimental (dimeticone) and local (sodium carbonate) treatments, aiming to assess the non-inferiority of local treatments of tungiasis among children, who are the key target-population of this disease. In addition, we will investigate further treatment strategies that apply to the local area.

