## 2. Experimental Design

### 2.1. Objectives

Main objective: To compare 5% sodium carbonate and dimeticone in the treatment of tungiasis among children in Kenya.

Specific objectives:(1)To compare the cure rates of the two treatments (5% sodium carbonate and dimeticone) within seven days.(2)To assess the safety of the two treatments by determining the incidence of adverse effects.(3)To compare the acute pathology scores of the two treatments.(4)To assess the acceptability of the two treatments in the community.

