### 3.2. Randomisation, Allocation, and Blinding

All study participants will receive 5% sodium carbonate and dimeticone, with one treatment per foot. Randomisation will be carried out at the treatment level and not the individual level. Trained nurses will perform the intervention. It is not possible to blind the intervener administering the treatment because 5% sodium carbonate will require soaking the foot, whereas NYDA^®^ will be applied directly to each lesion. As the two treatments will not change the skin colour of the feet, the principal investigator will be a blinded observer.

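### Section 4.4 admits local adverse events outside the acute pathology score to the secondary outcome only if investigators attribute them to treatment, and the adverse effects listed in section 2.6 cannot be compared between treatments

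*Protocol article*

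**What the plan says.** - **Objective 2** (protocol, section 2.1): "To assess the safety of the two treatments by determining the incidence of adverse effects". Section 4 (Expected Results) repeats the intent, listing differences in adverse effects among the secondary endpoints.
- **Endpoint list** (section 2.6): adverse effects are nausea or vomiting, arthralgia, fever, headache, fatigue or malaise, myalgia and chills. A separate secondary endpoint, the acute pathology score, covers pain, itching, erythema, warmness, oedema, desquamation, fissure, suppuration, ulcer, abscess and clustered lesions. Neither carries an attribution condition.
- **Recording** (section 4.4): "All adverse events, whether serious or non-serious, will be recorded until day 7".
- **What enters the outcome** (section 4.4): "Any adverse event that can be attributed to the intervention will be specified as a secondary outcome".
- **How relatedness is decided** (section 4.4): "The investigators will determine the relatedness of an event to the study treatment, based on a temporal relationship to the study treatment", and on whether the event is unexpected or unexplained given the child's course, history and other medication.
- **General symptoms** (section 4.4): the protocol states that "we cannot know which treatment might cause adverse effects with general symptoms", because every child receives both treatments. It adds that skin symptoms can be analysed by treatment.
- **Masking** (section 3.2): "It is not possible to blind the intervener administering the treatment". The principal investigator is named as a blinded observer.
- **Analysis** (section 4.1): generalized estimating equations for side effects, with pain and itching as the examples, and no attribution condition.

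**The concern.** Treatments are randomised to the two feet of the same child, so a count of all local events by foot compares the agents directly. No causality opinion is needed. Filtering by judged relatedness puts an opinion between the randomisation and the comparison. If attribution is more likely for one agent than for the other, equal event rates will be reported as different. A true reaction that looks like the disease may also be set aside as explained.

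The protocol gives an assessor unequal prior expectations. It writes of one agent that "Dimeticones are safe, since they are biochemically inert, non-toxic, non-carcinogenic, and non-teratogenic", and of the other that, if mishandled, "sodium carbonate can pose some hazards to health and safety".

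The second issue is consistency. Section 2.6 makes a list of systemic symptoms the adverse-effect endpoint. Section 4.4 makes attributed events the endpoint and says that general symptoms cannot be traced to either agent. Taken together, they leave the safety objective without a treatment comparison from the listed adverse effects.

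**Working it through.** The protocol gives no figure for this point, so there is nothing to reproduce. The check traces how each kind of event reaches a comparison.

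**Step 1. Routes into the outcome**

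| Kind of event | Stated route | Attribution condition | Comparison between feet |
|---|---|---|---|
| Systemic symptoms (section 2.6 list) | Adverse-effect endpoint | None in 2.6; required in 4.4 | Impossible, as 4.4 concedes |
| Local signs in the acute pathology score (2.6), with pain and itching also by GEE (4.1) | Own secondary endpoint | None | Possible, unfiltered |
| Local events not in the score, e.g. blisters, burning, dermatitis (named in 4.5) | The attribution sentence in 4.4 | Yes | Possible, but only for attributed events |

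Only the third row is affected by the filter. Only the first row has no comparison at all.

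**Step 2. Can the relatedness criteria separate the feet?**

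- Timing: section 3.3 describes both feet being washed and treated together, so the time from treatment to event is nearly the same for each.
- Unexplained course: every child has tungiasis, which itself produces skin signs. A local reaction can readily be put down to the disease.
- The foot on which the event occurred, which is the informative fact, is not a listed criterion.

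**Step 3. What the filter can do to the comparison**

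Let *r* be the true incidence of such local events, equal on both feet. Let *q*₁ and *q*₂ be the probabilities that an event on each foot is attributed.

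- Counted rates: *r q*₁ and *r q*₂
- Spurious risk difference: *r*(*q*₁ − *q*₂)
- Spurious relative risk: *q*₁ / *q*₂, whatever the value of *r*

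The protocol gives neither *r* nor *q*, so all values below are assumptions. With *r* = 10%:

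| *q*₁ | *q*₂ | Counted rates | Risk difference | Relative risk |
|---|---|---|---|---|
| 0.9 | 0.9 | 9% v 9% | 0 points | 1.00 |
| 0.9 | 0.7 | 9% v 7% | 2 points | 0.9/0.7 = 1.29 |
| 0.9 | 0.5 | 9% v 5% | 4 points | 0.9/0.5 = 1.80 |
| 0.6 | 0.3 | 6% v 3% | 3 points | 0.6/0.3 = 2.00 |

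At *r* = 5%, the second and third rows give differences of 1 and 2 points. At *r* = 20%, they give 4 and 8 points. The relative risk does not change with *r*. It only restates the assumed ratio of attribution probabilities, so the table shows the mechanism and does not estimate a bias in this trial.

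**The case against.** The strongest reply is that the attribution sentence must be read with what follows it. Section 4.4 goes straight on to say that general symptoms cannot be assigned to a treatment while skin symptoms can. On that reading, attributed simply means assignable to one foot, and the comparison by foot is already there. Local safety is also compared without any filter through the score and the GEE. What remains is narrow. Section 4.5 says that irritation, blisters and burning generally arise from eye contact or inhalation, and on the foot they would overlap with pain and erythema in the score. The GEE sentence gives pain and itching only as examples, so it might extend to other local effects.

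Much of this stands. A reader might infer that the whole foot-to-foot safety comparison rests on a causality opinion. The protocol does not support that, for the reasons just given. A reader might also infer that an unmasked person makes the judgement. The protocol does not say so: it assigns relatedness to the investigators, the principal investigator is the blinded observer, and the nurses' stated part is to monitor and to detect reactions so that the child gets care. The fair statement is that masking of this judgement is not stated, and a condensed article may leave it to the full protocol.

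Two things do not go away. The benign reading of attributed is possible, but the relatedness rule earlier in the same section defines the judgement by timing and unexplained course, not by foot. Saying that skin symptoms can be analysed by treatment does not say that every local event is counted. The conflict between sections 2.6 and 4.4 over systemic symptoms is untouched by the reply.

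**Conclusion.** The concern holds in a limited form. For local adverse events outside the acute pathology score, the only route stated into the secondary outcome is the investigators' attribution. That filter is unnecessary when treatment is randomised by foot, and it can bias the comparison if attribution differs by agent. Local signs inside the score are not affected.

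The adverse effects listed in section 2.6 offer no usable comparison between treatments for objective 2, and sections 2.6 and 4.4 have to be reconciled.

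The size cannot be estimated from the protocol. Any bias depends on unequal attribution, which is an assumption; with equal attribution the spurious relative risk is 1.0. Its direction is not known either, although the protocol's descriptions of the two agents suggest which way expectation might lean. This concerns a secondary outcome and does not touch the primary analysis. It is still worth settling before any relatedness judgement is made, because the safety findings would accompany the guideline recommendation that section 4 hopes for.

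**What to change.** Replace the attribution sentence in section 4.4 with wording such as:

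> All local (foot-level) adverse events from treatment to day 7 are a secondary outcome. They are counted by the foot on which they occur and compared within child, regardless of judged relatedness. The investigators' relatedness assessment is tabulated separately, is descriptive, and does not decide whether an event is counted. General symptoms are reported once per child without a comparison between treatments.

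Amend section 2.6 to match: name local adverse events as the comparative safety endpoint alongside the acute pathology score, and mark the systemic list as descriptive.

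The cost is a short edit to two sections and an extra table column. No new data are needed, since all events are already recorded to day 7. The downside is a somewhat higher background count, because some events due to the disease will be included on both feet.
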